## Ethical committee (EC)

This study will be submitted for formal review and approval to the Institutional Review Board of the Menzies School of Health Research, the Committee on Human Research (CHR) of the University of San Francisco (UCSF) and the Institutional Ethics Committees at ICDDR,B in Bangladesh. No participant will be enrolled or samples processed before written approval from these bodies is obtained.

## Declaration of Helsinki

The study will be carried out according to the principles stated in the Declaration of Helsinki (Ethical Principles for Medical Research Involving Human Subjects) as amended in 2008, all applicable regulations and according to established international scientific standards.

Any substantial amendments to the protocol or the Informed Consent Form (Annex VIII) will also be submitted for approval to the same ECs and competent authorities and will be implemented only after approval has been obtained.

## Expected benefits

Participants will be provided with a thorough physical examination. The outcome of the re-evaluation of national malaria treatment guidelines and the collection of indicative data on the safety of PQ treatment without prior G6PD testing will be of significant benefit to the local population.

## Potential risks

The study has an observational character: study drugs, treatment regimen and pre-treatment diagnostic tests are identical to national guidelines. Participating in the study does not pose an increased risk compared to standard treatment for the participant.

## Informed Consent (Annex VIII)

The information, consent and assent form will be translated to Bangla and back translated to English to ensure adequate translation. Written informed consent will be obtained from all participants or their legal guardians. Information provided during the consenting process will include description of the sample collection procedure, aim of the study, details on the data collected, potential benefits and risks and assurance of confidentiality for all information and results generated by the study. Legal representatives of enrolled children will be asked for written informed consent. Assent will be sought from all participants ≥11 years and <18 years.

After obtaining the G6PD results a second informed consent process will be conducted to ensure participants understand the potential risks and the expected benefits of Primaquine treatment

Information and consent form will be read out to all participants not fully literate; illiterate patients willing to participate will provide consent by a fingerprint in the presence of a witness.

## Withdrawing informed consent

All participants will be thoroughly informed about their right to withdraw consent at any time without having to provide a reason for withdrawal nor having to fear negative consequences. Data, samples and results collected prior to consent withdrawal will be destroyed.

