# Objective

**Primary:**

- To assess side effects observed following unsupervised PQ treatment in *P. vivax* and *P. falciparum* patients

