## Patient withdrawal and protocol violation

- Withdrawal of consent. A patient may withdraw consent at any time, without prejudice for further follow-up or treatment at the study site.
- Protocol violation (e.g. enrolment violation or incomplete treatment). Patients with any protocol violation will be followed up as scheduled for safety assessment. This also includes patients with serious adverse events that necessitate termination of treatment before the full course is completed.

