# Assessment of variables and statistical methodology

## Safety endpoints

- Proportion of patients with severe anaemia (Hb<7g/dl)
- Proportion of patients receiving blood transfusion
- Fractional change in Hb between baseline and day 6, 9,12,16, 23 and 30 (incl. proportion of patients with >25% drop in Hb between the timepoints)
- Proportion of patients with anaemia less than 7g/dl on day 3 and day 9
- Proportion of patients with adverse and serious adverse events

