# Sample Size

In 2013 a total of 142 vivax cases and 2190 falciparum cases were registered within the district of Alikadam with the majority of cases occurring during and after the monsoon season. The study hospital treated a total of 49 vivax cases and 432 falciparum cases in the same year. As the proposed study will be conducted during the peak malaria season we propose an enrolment target of approximately 50 vivax cases and 160 falciparum cases.

This study is part of a framework of comparable studies working with similar tools as proposed herein. Results for the primary objective will be pooled together with results of other sites to provide reliable results.

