# Ethical considerations

## Data Safety Monitoring Board (DSMB)

A DSMB will be formed at icddr,b to oversee all safty data in regular intervals. The PI in consultation with the IRB Secretariat of icdddr,b will form the DSMB Committee and the frequency of meetings will be agreed on with the Chairman, ERC. It is the principle investigators duty to provide regular reports to the DSMB in due time before the meeting. The DSMB can issue recommendations regarding the further conduct of the study

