***If no***

Principal reason for premature termination:

☐Patient vomited the study drug a second time and received rescue treatment before PQ was given

☐Early Treatment failure before PQ was given

☐Patient found to be severely G6PD deficient and excluded before PQ treatment was given

☐Patient withdrew consent

☐Lost to follow up

☐Death

☐ Other: please specify………………………………………………

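### Destroying all data from patients who withdraw consent deletes side effects already observed, and the records needed to check for bias go with them

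*Protocol*

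**What the plan says.** Section 9.7 (Withdrawing informed consent) gives participants the "right to withdraw consent at any time without having to provide a reason for withdrawal" and then sets the consequence for what has been collected: "Data, samples and results collected prior to consent withdrawal will be destroyed". It does not separate safety data from other data, or records from biological samples.

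The primary objective is "To assess side effects observed following unsupervised PQ treatment in" vivax and falciparum patients. The safety endpoints (Section 5.1) are mostly proportions: severe anaemia, transfusion, a haemoglobin (Hb) fall of more than 25%, and "Proportion of patients with adverse and serious adverse events". On size, Section 8 says "we propose an enrolment target of approximately 50 vivax cases and 160 falciparum cases".

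Four other places bear on the point:

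- Section 4.4.5 allows withdrawal of consent and, under a separate bullet on protocol violation, says "Patients with any protocol violation will be followed up as scheduled for safety assessment". That bullet also covers patients whose treatment is ended early because of a serious adverse event.
- Section 6 has the original data forms stored for as long as national law requires, with no exception for withdrawn patients.
- Section 9.6 plans a second consent step once the G6PD result is known, before PQ is handed out.
- The end-of-study form in Annex IX lists "Patient withdrew consent" among the reasons for early termination.

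**The concern.** The rule acts on events that have already been seen and written down. A vivax patient with a falling Hb on day 6 or day 9 who then withdraws consent would have that fall, and any adverse event or transfusion, removed from the study. The patient would leave the numerator and the denominator of each safety proportion.

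For a study about side effects, the worry is that withdrawal may be related to the outcome. If feeling ill on PQ prompts some withdrawals, the patients who remain have fewer events than the patients treated. No reason for withdrawal need be given, so such exits cannot be reliably identified. A statistical analysis plan cannot repair this, because it cannot analyse records that no longer exist. Section 8 also says that results for the primary objective will be pooled with other sites, so any distortion would carry into the pooled estimate.

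**Working it through.** **Nothing to reproduce.** The protocol states no withdrawal rate, no expected side-effect rate and no power calculation, and the enrolment target comes from case counts. The size can only be shown over assumed ranges.

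**Inputs from the protocol.** About 50 vivax and 160 falciparum patients, 210 in all (Section 8); deletion of everything collected before withdrawal (Section 9.7).

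**Assumptions.** True event rate p = 2% to 20%. Withdrawal risk without an event w0 = 2% to 10%. Withdrawal risk with an event w1 = r × w0, with r = 0.5, 1, 2 or 5.

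**Formula.** Expected reported rate after deletion = p(1 − w1) / [p(1 − w1) + (1 − p)(1 − w0)].

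**One case in full, p = 10% and w0 = 10%:**

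- r = 0.5: 0.095 / (0.095 + 0.81) = 10.5%
- r = 1: 0.09 / (0.09 + 0.81) = 10.0%
- r = 2: 0.08 / (0.08 + 0.81) = 9.0%
- r = 5: 0.05 / (0.05 + 0.81) = 5.8%

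**Over the whole assumed range:**

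| r | Relative change in the reported rate |
|---|---|
| 0.5 | rise of about 1% to 5% |
| 1 | none |
| 2 | fall of about 2% to 11% |
| 5 | fall of about 7% to 44% |

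For r = 2 and r = 5 the smallest fall is at p = 20%, w0 = 2% (19.67% and 18.67% reported). The largest is at p = 2%, w0 = 10% (1.78% and 1.12% reported).

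**Single patients in the vivax cohort (exact Clopper–Pearson 95% intervals):**

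- One event, record kept: 1/50 = 2.0% (0.1 to 10.6).
- Same event, record destroyed: 0/49 = 0% (0 to 7.3).

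One deletion moves the estimate by about 2 percentage points and turns an observed event into none observed. In the falciparum cohort the same deletion changes 1/160 = 0.6% to 0/159 = 0%.

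**Withdrawal before PQ.** If 5 of 50 leave at the second consent and 5 events occur among the other 45, deletion gives 5/45 = 11.1%, against 5/50 = 10.0% with all enrolled patients in the denominator. This shift runs upward. It is a matter of denominator, since those five never received PQ.

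**The case against.** The strongest reply is that the direction of bias is not in the documents. A reader might infer that every safety proportion is biased towards safety. The protocol does not support that: it gives neither the frequency of withdrawal nor the reasons. The bias is zero if withdrawal is unrelated to events, and the reported rate rises if patients with events withdraw less often or if exits come before PQ. This objection stands.

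Nor is withdrawing consent the only way out for a patient who feels ill. PQ is unsupervised, so tablets can simply be stopped. The symptom form has a box for stopping PQ, and Section 4.4.5 keeps patients whose treatment ends early in safety follow-up. Section 9.7 does not order destruction for those lost to follow-up. This limits how many events the rule would reach, but it does not protect the events of patients who do withdraw consent.

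A reader might also see a contradiction with Section 4.4.5, or with Section 9.1, where "A DSMB will be formed at icddr,b to oversee all safty data in regular intervals". Neither is strict. The follow-up rule belongs to protocol violations, which are listed apart from consent withdrawal, and periodic oversight by a DSMB does not promise permanent retention.

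It is also tempting to say that no trace would remain. The end-of-study form records withdrawal as a reason. If that count survives, bounds are possible: with 3 events in 48 and 2 withdrawn, the rate lies between 3/50 = 6.0% and 5/50 = 10.0%. The protocol does not say whether the form survives.

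Finally, an example such as 5/50 = 10.0% becoming 3/48 = 6.25% is an extreme case. It has 2 of 5 event patients withdrawing and no event-free patient doing so. Two event-free withdrawals instead give 5/48 = 10.4%.

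Destruction on withdrawal is also a protection offered to participants and goes to three ethics bodies (Section 9.2). That is a reason to change it openly. It does not remove the statistical cost.

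**Conclusion.** The point holds in this form: Section 9.7 deletes observed safety events from a study whose primary objective is side effects, and nothing elsewhere in the protocol exempts them. The defect does not depend on which way the bias runs. The individual records that would show its direction and size are the ones destroyed.

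Understatement follows only if withdrawal is related to side effects. That is plausible, but it is an assumption. How large it would be rests on the assumed event rates, withdrawal rates and withdrawal ratios, not on protocol figures. A twofold ratio costs little; a fivefold ratio can remove up to about two fifths of the reported rate. In the vivax cohort even one deletion matters.

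What remains between Section 9.7 and the end-of-study form, and between Section 9.7 and the form-storage rule in Section 6, is unreconciled text rather than outright contradiction. The protocol should say which rule governs. It should be changed, and this cannot be deferred to the analysis stage.

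**What to change.** Before enrolment, and subject to ethics approval:

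- Revise Section 9.7 and the consent and assent wording so that coded data collected up to withdrawal, at least adverse and serious adverse events, Hb and transfusions, are kept and included in the safety analysis. No new data are collected after withdrawal, and stored samples are destroyed on request.
- Report the number and timing of withdrawals, separating those before PQ from those after it.
- Reconcile Section 9.7 with the end-of-study form in Annex IX and with the form-storage rule in Section 6.

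The cost is a paragraph in the protocol, matching consent text and an ethics submission. The consent forms are not in the text at hand, so their present wording could not be checked. The real downside is that the promise to participants changes. That is why it belongs before enrolment: data promised for destruction cannot fairly be kept later. The right to withdraw without giving a reason is untouched, and Section 9.8 already has data held under study identification numbers.

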## Confidentiality

No identifying information will be made public. Identities of all participants are coded with a study identification number (study ID). Only the investigators will have the key that link study ID number to the patient identity.

The study works with a database. Participant data entered into the database is identified through assigned study IDs and the database is password protected. All data analysis is done on the database with the study ID numbers, stored isolates and samples are labelled with the study ID number only. If isolates or samples are shipped to reference laboratories for additional analysis, only study ID number, but not the full name is provided to the receiving organization. Participant’s study information will not be released to anybody outside the medical and research team, except as necessary (and under confidentiality agreement) for the independent monitoring, auditing and for inspection by competent authorities.

## Monitoring and Quality Control

Quality assurance and monitoring will be conducted in regular intervals. Procedural and reagents controls will be provided throughout the study period. Performance of laboratory technicians is assured by on-site training and site visits through the icddr,b and the MSHR. Site-visits are foreseen by the investigators on a regular basis, as well as weekly e-mail or Skype communication with local study staff.

# Publication Policy

All Investigators will be involved in reviewing drafts of the manuscripts, abstracts, press releases and any other publications arising from the study. Authorship will be determined in accordance with the ICMJE guidelines and other contributors will be acknowledged.

# Overview Annexes:

- Annex I: Drugs with antimalarial activity
- Annex II: Severe malaria
- Annex III: Dosing for AL
- Annex IV: Dosing for CQ
- Annex V: Dosing for PQ
- Annex VI: Dosing of 2^nd^ line treatment and treatment for severe malaria
- Annex VII: Definition of treatment failures.
- Annex VIII: Consent Forms
- Annex IX: Case Record Forms
- Annex X: Signs and Symptom for unscheduled visit
- Annex XI: timeline

# Annex I

**Drugs with antimalarial activity that should not be used during the study**

- Proguanil, Chlorproguanil, Pyrimethamine
- Sulfadoxine, Sulfalene, Sulfamethoxazole, Dapsone
- Atovaquoneantibiotics: Tetracycline*, Doxycycline, Erythromycin, Azythromycin, Clindamycin, Rifampicin, Trimethoprim
- Pentamidine

* Tetracycline eye ointments can be used.

# Annex II

**Signs or Symptoms Indicative of Severe Malaria**

- impaired consciousness, including unrousable coma (Blantyre Coma Score <5, GCS<15)
- prostration, i.e. generalized weakness so that the patient is unable to sit, stand or walk without assistance
- multiple convulsions: more than two episodes within 24h
- deep breathing and respiratory distress (acidotic breathing)
- acute pulmonary oedema and acute respiratory distress syndrome
- circulatory collapse or shock, systolic blood pressure
- < 80mm Hg in adults and < 50mm Hg in children
- acute kidney injury
- clinical jaundice plus evidence of other vital organ dysfunction
- Bleeding Disorder (Epistaxis, bleeding gums, frank haematuria)

For further reference see the Third Edition of the WHO publication “Management of severe malaria – A practical handbook”

<http://www.who.int/malaria/publications/atoz/9789241548526/en/index.html>

# Annex III

**Drug dosing for AL (Coartem)**

| **Drug** | **Day** | **Weight in kg** | | | |
| --- | --- | --- | --- | --- | --- |
|  |  | **6-14kg*** | **15-24kg** | **25-34kg** | **≥34+kg** |
| **Tab Coartem**  Arthemether 20 mg + Lumefantrine 120mg | **Day 0a**  **Day 0b** | 1  1 | 2  2 | 3  3 | 4  4 |
|  | **Day 1a**  **Day 1b** | 1  1 | 2  2 | 3  3 | 4  4 |
|  | **Day 2a**  **Day 2b** | 1  1 | 2  2 | 3  3 | 4  4 |

**For children under 5kg Coartem is not recommended according to the national guidelines (instead they receive Quinine 300mg 1/4 tablet for 7days). Children under 6kg (Revised malaria treatment Regimen 2009 DGHS) are excluded from this study.

# Annex IV

**Dosing schedule CQ**

Total dose - 25 mg/ kg body weight

| **Drug** | **Day** | **Weight in kg*** | | | | | |
| --- | --- | --- | --- | --- | --- | --- | --- |
|  |  | **6-9** | **10-19** | **20-29** | **30-39** | **40-49** | **50+** |
| **Tab CQ**  **150mg**  **Base** | **Day 0** | **1/2** | **1** | **1 1/2** | **2** | **3** | **4** |
|  | **Day 1** | **1/2** | **1** | **1 1/2** | **2** | **3** | **4** |
|  | **Day 2** | **1/2** | **1** | **1 1/2** | **2** | **2** | **2** |

*For children unable to swallow the tablets, they will be crushed in water. No syrup formulation available in Bangladesh

# Annex V

Primaquine (PQ) dose regimen

| **Drug** | **P.v. / P.f.** | **Day** | **Weight in kg** | | | | | |
| --- | --- | --- | --- | --- | --- | --- | --- | --- |
|  |  |  | **6-9** | **10-19** | **20-29** | **30-39** | **40-49** | **>50** |
| **Tab Primaquine 15 mg** | Treatment in P.v. cases | 3-16 | 1/4 | 1/2 | 1 | 1 | 1 | 1 |
|  | Treatment for P.f. cases | 3 (unsupervised) | 1/2 | 1 | 1 1/2 | 2 | 2 1/2 | 3 |

# Annex VI

Dosing of 2^nd^ line treatment and treatment for severe malaria

|  | drug | dosage |
| --- | --- | --- |
| P.f. 2^nd^ line treatment | Quinine (tablets) | 10mg/kg every 8 hours for 7 days |
| P.f. 3^rd^ line treatment | Quinine (tablets) + tetracycline | Q: 10mg/kg every 8 hours for 7 days  T: 250mg every 6 hours for 7 days |
|  | Quinine (tablets) + doxycycline | Q: 10mg/kg every 8 hours for 7 days  C: 100mg every 12 hours for 7 days |
| Severe malaria | Quinine IV/IM + quinine (tablets) | IV/IM: 10mg?kg followed by  Oral: Q: 10mg/kg every 8 hours for 7 days |
|  | Arthemether (IM) or artesunate (IV) followed by AL oral | 2.4mg/kg at H0, H12, H24 followed by Coartem daily for 3 days as indicated in Annex III |

# Annex VII

Definition of Treatment Failure

**Early treatment failure**

• Danger signs or severe malaria on day 1, 2 or 3 in the presence of peripheral parasitaemia;

• Parasitaemia on day 2 higher than on day 0, irrespective of axillary temperature;

• Parasitaemia on day 3 with axillary temperature ≥ 37.5 ºC;

• Parasitaemia on day 3 ≥ 25% of count on day 0.

**Late treatment failure**

**Late clinical failure**

• Danger signs or severe malaria in the presence of parasitaemia on any day between day 4 and last day of Follow up in patients who did not previously meet any of the criteria of early treatment failure;

• Presence of parasitaemia on any day between day 4 and the last day of follow up with axillary temperature ≥ 37.5 ºC (or history of fever) in patients who did not previously meet any of the criteria of early treatment failure

**Late parasitological failure**

Presence of parasitaemia on any day between day 7 and the last day of follow up with axillary temperature < 37.5 ºC in patients who did not previously meet any of the criteria of early treatment failure or late clinical failure

#

**Annex IX**

**Case record form**

**Date of Birth:** **OR** **Age:** ☐☐ in ☐ Month ☐ Year

D

D

M

M

Y

Y

Y

Y

**Sex:** ☐ Male ☐ Female **Ethnicity:** ☐ Tribal ☐ Non Tribal

**If tribal**, which tribe? ☐ Marma ☐ Chakma ☐ Tripura ☐ Tanchangya ☐ Khyang ☐ Bawm ☐ Rakhaine ☐ Mro ☐ Pangkho ☐ Lusai ☐ Khumi ☐ Chak ☐ Other (specify) _______________________

**Day – 0 Date of visit:** ☐☐-☐☐-☐☐☐☐

1. **Weight:** ☐☐☐.☐ Kg

2. **Temperature:** ☐☐.☐ ˚C

3. **Finger prick (baseline) collected?** ☐ Yes ☐ No

*If yes:* **Blood slide (baseline) collected?** ☐ Yes ☐ No

*If yes:* Time: ☐☐:☐☐ in 24:00 format (e.g. 4pm is 16:00)

**Parasite count (baseline):** ________/500RBC or ___________/200WBC

**Diagnosis:** ☐ Pf ☐ Pv ☐Mixed

*If yes:* **Hemoglobin (baseline) measured?** ☐ Yes ☐ No

*if Yes:* ☐☐.☐ g/dl

4. **Venous blood (baseline) collected?** ☐ Yes ☐

5. **Does this patient have a family history of hemolysis (severe anemia)?** ☐ Yes ☐ No ☐Uncertain

*If yes, was it in response to:*  ☐Medication ☐Food ☐Infection ☐Other

6. **Does this patient have a family history of G6PD deficiency?** ☐ Yes ☐No ☐ Uncertain

7. **Has this patient ever had a blood transfusion?** ☐ Yes ☐ No

*If yes, within the last 12 weeks?* ☐ *Yes* ☐ *No* ☐ *Uncertain*

8. **2^nd^ Blood slide collected?** ☐ Yes ☐ No

*If yes:* Time: ☐☐:☐☐ in 24:00 format (e.g. 4pm is 16:00)

**Parasite count:** ________/500RBC or ___________/200WBC

**Diagnosis:** ☐ Pf ☐ Pv ☐Mixed

9. **Schizontocidal Treatment**

| Schizontocidal treatment | Pf | Pv | mixed |
| --- | --- | --- | --- |
| 1^st^ Dose (observed) | AL given  ☐ Yes ☐ No ☐  Dose:___________ | CQ given  ☐ Yes ☐ No ☐  Dose:___________ | AL given  ☐ Yes ☐ No ☐  Dose:___________ |
| 2^nd^ Dose | AL given  ☐ Yes ☐ No ☐  Dose:___________ | N/A | AL given  ☐ Yes ☐ No ☐  Dose:___________ |
|  | Was this dose given as observed treatment  ☐yes ☐no |  | Was this dose given as observed treatment  ☐yes ☐no |

**Day – 1 Date of visit:** ☐☐-☐☐-☐☐☐☐

10. **Temperature:** ☐☐ **.** ☐˚C

11. **Finger prick collected?** ☐ Yes ☐ No

*If yes:* **Blood slide collected?** ☐ Yes ☐ No

*If yes:* Time: ☐☐:☐☐ in 24:00 format (e.g. 4pm is 16:00)

**Parasite count:** ________/500RBC or ___________/200WBC

*If yes:* **Hemoglobin measured?** ☐ Yes ☐ No

*if Yes:* ☐☐.☐ g/dl

12. **2^nd^ Blood slide collected?** ☐ Yes ☐ No

*If yes:* Time: ☐☐:☐☐ in 24:00 format (e.g. 4pm is 16:00)

**Parasite count :**________/500RBC or ___________/200WBC

13. **Schizontocidal Treatment**

| Schizontocidal treatment | Pf | Pv | mixed |
| --- | --- | --- | --- |
| 1^st^ Dose (observed) | AL given  ☐ Yes ☐ No ☐  Dose:___________ | CQ given  ☐ Yes ☐ No ☐  Dose:___________ | AL given  ☐ Yes ☐ No ☐  Dose:___________ |
| 2^nd^ Dose | AL given  ☐ Yes ☐ No ☐  Dose:___________ | N/A | AL given  ☐ Yes ☐ No ☐  Dose:___________ |
|  | Was this dose given as observed treatment  ☐yes ☐no |  | Was this dose given as observed treatment  ☐yes ☐no |

**Day – 2: Date of visit:** ☐☐-☐☐-☐☐☐☐

14. **Temperature:** ☐☐.☐˚C

15. **Finger prick collected?** ☐ Yes ☐ No

*If yes:* **Blood slide collected?** ☐ Yes ☐ No

*If yes:* Time: ☐☐:☐☐ in 24:00 format (e.g. 4pm is 16:00)

**Parasite count** ________/500RBC or ___________/200WBC

*If yes:* **Hemoglobin measured?** ☐ Yes ☐ No

*if Yes:* ☐☐.☐ g/dl

16. **2^nd^ Blood slide collected?** ☐ Yes ☐ No

*If yes:* Time: ☐☐:☐☐ in 24:00 format (e.g. 4pm is 16:00)

**Parasite count** ________/500RBC or ___________/200WBC

